### Statistical analyses

All analyses will be conducted in agreement with the intention-to-treat principle. Descriptive statistics will be used to describe the sociodemographic characteristics, health-related characteristics of the partner, the health situation of the patient with cancer, and the outcome measures. Chi-square tests and independent samples t-tests will be used to analyze whether randomization resulted in a balanced distribution of sociodemographic and health-related characteristics across the study arms. Mann–Whitney U tests will be performed in case of non-normality of the data. To test whether there are differences in the outcomes across the study arms at baseline, independent samples t-tests will be used.

Linear mixed models (LMM) will be used to determine the efficacy of Oncokompas by comparing longitudinal changes between the intervention group and control group with fixed effects for study arm, time, and their two-way interaction, as well as a random intercept for individuals.

LMM will also be used to determine whether age, gender, socioeconomic status (e.g. education level and work situation), the health situation of the patient, and baseline quality of life moderate the efficacy of Oncokompas with fixed effects for study arm, time, the potential moderator, and all two-way and three-way interaction effects, as well as a random intercept for individuals.

Post-hoc analyses will be applied when significant results are found in the efficacy and moderation analyses. To measure the differences in change between the intervention group and control group at follow-up measurements, independent samples t-tests with Bonferroni correction will be used. These tests will also be used to assess whether change scores between the intervention group and control group differed significantly within each category of the significant moderator variables.

The effect sizes (ES) of the intervention will be measured by calculating the (between group) Cohen’s d. The magnitude of the ES is classified as large (≥ 0.80), moderate (0.50–0.79) or small (< 0.50) [41].

A *p* value < 0.05 will be considered significant for all analyses. All tests will be one-tailed. IBM Statistical Package for the Social Sciences (SPSS) version 26 (IBM Corp., Armonk, NY USA) will be used to perform all statistical analyses.

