#### Partners who want to participate

Partners meeting the inclusion and exclusion criteria will receive an information package by post (consisting of an information letter, an informed consent form, and a reply envelope). If partners want to participate in the study, they are asked to return the signed informed consent form using the reply envelope. After the coordinating researcher has received the signed informed consent form, this researcher will send partners a link to the online baseline questionnaire by e-mail. After completion of the first questionnaire, partners will be randomized into the intervention group or the control group. Partners randomized to the intervention group will receive an invitation e-mail for Oncokompas to activate their personal account. Partners randomized to the control group will receive an e-mail to activate their account after completion of the last questionnaire (t2).

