### Outcome assessment

Caregiver burden is the primary outcome measure used to assess the efficacy of Oncokompas among partners of patients with incurable cancer. Secondary outcome measures are general self-efficacy and health-related quality of life. In addition, outcomes on cost-utility will be measured.

Measurements will be collected at baseline (t0), two weeks after randomization (t1), and three months after the baseline measurement (t2). Measurements will be assessed through online questionnaires. An overview of the primary and secondary outcome measures is shown in Table 3.

**Table 3 Tab3:** Measurement overview

Aim		Outcome measures	Instrument
Efficacy	Primary outcome measure Secondary outcome measures	Caregiver Burden Self-efficacy	Caregiver Strain Index + (CSI+) General Self-Efficacy Scale (GSE)
Cost-utility		Health-related quality of life Medical costs Productivity costs Costs of Informal Care	EuroQol 5 Dimensions (EQ-5D-5L) iMTA Medical Consumption Questionnaire (iMCQ) iMTA Productivity Cost Questionnaire (iPCQ) iMTA Valuation of Informal Care Questionnaire (iVICQ)

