### Sample size

To demonstrate the presence of an effect on the CSI+ of at least 0.5 standard deviations as statistically significant in a one-tailed test at alpha = 0.05 and a power of (1 - beta) = 0.80, a minimum of 51 participants in each condition of the RCT will be required at follow-up. Anticipating a drop-out rate of 25% between t0 and t2, 68 participants per condition need to be included at t0. Therefore, the total study cohort comprises 136 partners of patients with incurable cancer.

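### The efficacy model estimates a baseline arm difference that is zero by design, so it gives up precision that a common-baseline or baseline-adjusted model would recover at no cost

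*Protocol article*

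**What the plan says.** Statistical analyses in the Protocol article gives the efficacy model in full: a linear mixed model "comparing longitudinal changes between the intervention group and control group with fixed effects for study arm, time, and their two-way interaction". The only random effect is one intercept per person. The t0 measurement is therefore one of the modelled outcomes, and each arm has its own t0 mean.

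If the model is significant, contrasts follow: "To measure the differences in change between the intervention group and control group at follow-up measurements, independent samples t-tests with Bonferroni correction will be used". For the baseline values the section plans a test, but no adjustment: "To test whether there are differences in the outcomes across the study arms at baseline, independent samples t-tests will be used".

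The order of events is set under Partners who want to participate: "After completion of the first questionnaire, partners will be randomized into the intervention group or the control group". Outcomes are measured at t0, t1 and t2 (Outcome assessment).

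Sample size plans for "an effect on the CSI+ of at least 0.5 standard deviations". The calculation is one-sided at alpha 0.05 with 80% power. This gives 51 per arm at follow-up, 68 per arm after allowing for 25% dropout, and 136 in total. The document states neither an SD nor a correlation between CSI+ measurements.

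**The concern.** Since t0 precedes allocation, any t0 difference between the arms is chance. A model that estimates it freely spends information on a quantity already known to be zero in expectation. It then subtracts the whole observed t0 difference from the follow-up difference, where the efficient weight is only ρ. A baseline covariate, or a common t0 mean for both arms, applies the efficient weight.

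The trial is small, is planned at 80% power and expects to lose a quarter of its participants. A needlessly wide standard error on caregiver burden, and on the secondary outcomes analysed the same way, therefore matters.

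**Working it through.** **Inputs from the document:** effect 0.5 SD, one-sided alpha 0.05, power 0.80, 51 per arm at follow-up, 68 per arm randomised, 1:1 allocation, and a random intercept (so one common correlation ρ between any two time points).

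**Assumptions:** ρ, shown over 0.3 to 0.8; the timing of dropout; and, for power only, that 0.5 SD means SD of raw CSI+ scores.

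**1. The planned sample size.** The normal approximation gives 2(1.645 + 0.842)²/0.5² = 49.5, so 50 per arm. The exact one-sided t-test gives 51 (power 0.806). Then 51/0.75 = 68 and 2 × 68 = 136. The planned figures reproduce as a plain two-sample comparison.

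**2. Complete data.** In units of 2σ²/n, the variance of the t2 effect is:
- free t0 means (planned model): 2(1 − ρ)
- common t0 mean, or baseline as covariate: 1 − ρ²

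The cut is 1 − (1 + ρ)/2 = (1 − ρ)/2, which is positive for every ρ below 1.

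**3. With the planned dropout.** The mixed model keeps dropouts' data, which narrows the gap. Suppose first that all 17 per arm give t0 only. The free model's t2 effect equals the baseline-adjusted difference minus (1 − ρ) times the observed t0 difference among all 68 per arm. In units of 2σ²/51:
- common t0 mean: 1 − ρ²
- free t0 means: (1 − ρ²) + (51/68)(1 − ρ)²

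| ρ | free | common | variance cut | planned SE larger by |
|---|---|---|---|---|
| 0.3 | 1.278 | 0.910 | 29% | 19% |
| 0.4 | 1.110 | 0.840 | 24% | 15% |
| 0.5 | 0.938 | 0.750 | 20% | 12% |
| 0.6 | 0.760 | 0.640 | 16% | 9% |
| 0.7 | 0.578 | 0.510 | 12% | 6% |
| 0.8 | 0.390 | 0.360 | 8% | 4% |

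For example, at ρ = 0.4 the free model has 0.84 + 0.75 × 0.36 = 1.11, and the cut is 0.27/1.11 = 24%. If all 17 dropouts also give t1, the cuts at ρ = 0.4, 0.5 and 0.6 are 25%, 20% and 16%. Dropout timing therefore matters little.

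**4. Power of the t2 contrast,** as Φ(0.5/√Var − 1.645) with σ = 1. Here 10 dropouts per arm are assumed to give t0 only and 7 to give t0 and t1.

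| ρ | planned model | common t0 mean |
|---|---|---|
| 0.3 | 72% | 84% |
| 0.4 | 78% | 87% |
| 0.5 | 84% | 90% |
| 0.6 | 90% | 94% |

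At ρ = 0.4, for example, the variances are 0.0432 and 0.0326. The planned model gives 0.5/0.208 − 1.645 = 0.76, hence 78%. The constrained model gives 0.5/0.181 − 1.645 = 1.12, hence 87%. The planned model crosses 80% at ρ of about 0.44.

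**The case against.** The strongest reply is that arm, time and their interaction with a random intercept is a conventional analysis. It is unbiased under randomisation, it does use the baseline, and above ρ of about 0.44 it exceeds the planned power. All of that stands. It makes the point one of efficiency, and the document does not support several stronger readings that a reader might infer.

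- **A fixed percentage loss.** The cut depends on ρ, which the document does not report, and slightly on when participants drop out. Only a conditional range can be given.
- **Power below 80% whenever ρ is below 0.5.** That applies to a completers-only change-score t-test at 51 per arm, with 68%, 74% and 81% power at ρ = 0.3, 0.4 and 0.5. In the plan those t-tests are post hoc. Efficacy rests on the mixed model, which also uses dropouts' data.
- **A contradiction with the sample size.** Sample size does not say whether the 0.5 SD is of raw scores or of change. If it is of change, 51 per arm fits a change analysis.
- **Bias from regression to the mean.** A chance t0 imbalance shifts the estimate in a given trial, but it does not bias the estimator or invalidate the test over repeated randomisation.

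The article also does not name t2 as the single decisive contrast. If the overall interaction (2 degrees of freedom) is tested, the loss depends on the effect at t1. At ρ = 0.5 with complete data it is 11% for an effect at t2 only and 33% for equal effects at t1 and t2. The size changes, but the direction does not.

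**Conclusion.** The point holds as a free improvement; it does not show an error. The article fixes a model with free t0 means although its own procedures put the baseline before allocation, so this choice is stated and not simply left to a fuller document. Under a common correlation and the planned 25% dropout, the planned model's standard error at t2 is about 9-15% larger than necessary for ρ between 0.6 and 0.4. The direction of the gain is certain for any ρ below 1; its size rests on an unreported ρ. A shortfall from the planned power is a possibility confined to ρ below about 0.44, and only if the 0.5 SD is on the raw scale. In the same range of ρ (0.3 to 0.6) the constrained model stays at 84% or above.

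**What to change.** Prespecify one of two models for the CSI+, the GSE and the EQ-5D:

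- a baseline-constrained mixed model with time and arm-by-time effects at t1 and t2 only, and no arm effect at t0; or
- a mixed model on t1 and t2 with the baseline value as covariate, which is nearly equivalent when data are missing.

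For the first, code the arm variable as zero for everyone at t0. Deleting the arm main effect while keeping a full arm-by-time factor would only re-express the same unconstrained model.

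Replace the post-hoc change-score t-tests by the baseline-adjusted t1 and t2 contrasts from that model, keeping the Bonferroni correction. Do not let the baseline t-tests decide whether to adjust. State in Sample size which SD the 0.5 refers to, and the correlation assumed.

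The cost is a few lines of model syntax and a short amendment to the analysis text. No participants, visits or questionnaires are added. The article reports recruitment as still ongoing, so the change can be fixed before the data are analysed.

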## Methods/Design

### Study design

A prospective RCT with two parallel groups will be conducted to determine the efficacy and cost-utility of Oncokompas among partners of patients with incurable cancer.

Partners will be randomly assigned to the intervention group or the waiting-list control group. Partners in the intervention group will get direct access to Oncokompas, while partners in the control group will get access to the intervention three months after the baseline measurement (i.e. after completion of the last questionnaire). Partners will receive three questionnaires: at the time of inclusion (t0), two weeks after randomization (t1), and three months after the baseline measurement (t2). Figure 1 shows the flow diagram of the RCT. Figure 2 shows the schedule of enrollment, intervention, and assessments (according to the Standard Protocol Items: Recommendations for Intervention Trials (SPIRIT), see Additional file 1).

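### The random-intercept model assumes one common correlation across waves about 2, 11 and 13 weeks apart; if correlation falls with time, its three-month standard error is modestly too small

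*Protocol article*

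**What the plan says.** The protocol article, Statistical analyses, tests efficacy with a linear mixed model that has fixed effects for study arm, time "and their two-way interaction, as well as a random intercept for individuals". The moderator models carry the same random term. No residual covariance structure, random slope or robust standard error is named.

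Under Study design, the three questionnaires fall "at the time of inclusion (t0), two weeks after randomization (t1), and three months after the baseline measurement (t2"). Taking three months as 13 weeks, and randomization as following soon after baseline, the gaps are about 2 weeks (t0 to t1), 11 weeks (t1 to t2) and 13 weeks (t0 to t2).

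Two further statements bear on the point. "Post-hoc analyses will be applied when significant results are found in the efficacy and moderation analyses", and for the differences in change at the follow-ups "independent samples t-tests with Bonferroni correction will be used". Also, "All tests will be one-tailed".

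**The concern.** A random intercept with independent residuals gives every wave the same variance and every pair of waves the same correlation. Measurements two weeks apart may well correlate more strongly than measurements three months apart, and burden may become more variable over time. In that case the fitted common correlation lies above the true t0–t2 correlation and below the true t0–t1 correlation. The model then understates the standard error of the three-month change and overstates that of the two-week change.

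At stake are the size of a one-tailed 5% test of a three-month coefficient or a linear arm-by-time slope, and the width of the interval reported with it. The sample size section counts participants at the end of follow-up, so three months is where this matters most.

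**Working it through.** **The plan's own figure.** The Sample size section assumes "an effect on the CSI+ of at least 0.5 standard deviations" in a "one-tailed test at alpha = 0.05 and a power of (1 - beta) = 0.80". With the noncentral t distribution, power is 0.7989 at 50 per arm and 0.8059 at 51, so "a minimum of 51 participants in each condition of the RCT will be required at follow-up" reproduces. Then 51 / 0.75 = 68 per arm, or 136 in total. This calculation does not involve the covariance structure, so the point leaves it untouched.

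**Inputs.** The covariance model and wave timing come from the article. The correlations r01 (t0–t1), r12 (t1–t2) and r02 (t0–t2) are assumptions over a range, because the article gives none.

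**Formulas.** With complete data and equal variances σ²:
- variance of a person's change used by the model: 2σ²(1 − mean r), for any pair of waves
- true variance of the t0–t2 change: 2σ²(1 − r02)
- model SE / true SE at three months: √[(1 − mean r)/(1 − r02)]
- model SE / true SE at two weeks: √[(1 − mean r)/(1 − r01)]
- true one-sided size at three months: 1 − Φ(1.645 × three-month ratio)

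Example with r01 = 0.80, r12 = 0.60, r02 = 0.50: mean r = 1.90/3 = 0.633. The three-month ratio is √(0.367/0.50) = 0.856, so the size is 1 − Φ(1.409) = 8.0%. The two-week ratio is √(0.367/0.20) = 1.354. With 51 per arm and σ = 1, the model SE at three months is √(4 × 0.367/51) = 0.170, against a true √(4 × 0.50/51) = 0.198.

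| r01, r12, r02 (assumed) | SE ratio, 3 months | One-sided size, 3 months | SE ratio, 2 weeks | Size of joint 2-df test |
|---|---|---|---|---|
| 0.60, 0.60, 0.60 | 1.00 | 5.0% | 1.00 | 5.01% |
| 0.70, 0.65, 0.60 | 0.94 | 6.2% | 1.08 | 5.11% |
| 0.75, 0.60, 0.55 | 0.90 | 6.9% | 1.21 | 5.41% |
| 0.80, 0.65, 0.60 | 0.89 | 7.2% | 1.26 | 5.55% |
| 0.80, 0.60, 0.50 | 0.86 | 8.0% | 1.35 | 5.88% |

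The last column comes from the eigenvalues of the true contrast covariance relative to the model's residual variance. Letting the variances rise as well (1, 1.1, 1.3, with correlations 0.75, 0.65, 0.60) gives a three-month ratio of 0.91 and a size of 6.8%.

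**Simulation, complete data.** With 51 per arm and 20,000 null trials, the three-month coefficient had a one-sided size of 7.8% for 0.80, 0.60, 0.50, and 5.0% for equal correlations.

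**Simulation, with dropout.** With 68 per arm, 25% missing completely at random at t2 and 2,000 runs, the sizes for rows 1, 2, 4 and 5 of the table were 6.0%, 5.6%, 6.5% and 8.5%, with SE ratios of 0.97, 0.95, 0.89 and 0.84. The Monte Carlo error of a 5% rate here is √(0.05 × 0.95/2000) = 0.5 percentage points. These runs confirm the direction and rough size only.

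**Linear time instead of a wave-specific coefficient.** In simulation with 0.80, 0.60, 0.50, the one-sided size of the slope was 7.9% with time coded 0, 1, 2, and 8.9% with time in weeks (0, 2, 13). A direct check of the latter uses slope weights −5, −3, 8, whose squares sum to 98. The model variance is 98 × 0.367 = 35.9. The true variance is 98 + 2(15 × 0.80 − 40 × 0.50 − 24 × 0.60) = 53.2. The ratio is √(35.9/53.2) = 0.82, and the size is 1 − Φ(1.35) = 8.8%.

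**The two-step procedure.** This was simulated with categorical time, a joint 2-df interaction test as gate, then one-sided change-score t-tests with Bonferroni correction over two follow-ups (51 per arm, complete data, 40,000 null trials). With 0.80, 0.60, 0.50, the gate rejected in 6.0% of trials, and a false three-month claim survived both steps in 2.3%. With 0.70, 0.60, 0.50, the figures were 5.2% and 1.8%. This fits the Bonferroni level of 5%/2 = 2.5% per follow-up, which a gate can only lower.

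**The case against.** The strongest case against is that a reader might infer that the three-month standard error is wrong and the trial's three-month conclusion anti-conservative. The article does not support that. It gives no correlation, and no variance by wave, for the CSI+. If these are equal across waves, the model is right. The follow-up comparisons are t-tests on change scores, whose standard errors come from the observed changes. On the two-step reading, with a joint interaction test as gate, false three-month claims stay at about 2%. The article also does not say that the t2 coefficient is the decision rule. Finally, it is a condensed account that does not exclude a residual structure set out in an analysis plan that is not shown.

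Most of this stands and limits the point to its conditional form. Three things remain. First, the article does state a covariance model and repeats it for the moderators, so this is a choice made in the text and not merely a detail left out. Reading the residuals as independent is an inference, but a natural one. Second, the article makes every test one-tailed. A joint 2-df test has no direction, so a single-degree-of-freedom term is a natural reading of the efficacy test, and there the inflation applies in full. Third, the t-tests run only after a significant mixed model and need both measurements from each participant, with 25% dropout expected. The mixed model is therefore the gate, and it is the analysis that uses all available data.

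**Conclusion.** The point holds conditionally and is modest in size. With a random intercept as the only covariance term and independent residuals, and if correlation falls with the time gap, the model standard error of the three-month arm-by-time coefficient is about 6% to 14% too small. Its one-sided size is then about 6% to 8% at a nominal 5%, and up to 8.9% for a linear slope in weeks. The two-week standard error is 8% to 35% too large. These ranges rest on assumed correlations.

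The conclusion covers single-degree-of-freedom mixed-model terms and their intervals. It does not extend to a joint interaction test beyond about one percentage point, to the standard errors of the change-score t-tests, or to the sample size. It is worth correcting before analysis because the assumption suits these unequal gaps poorly and is easily avoided.

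**What to change.** In the efficacy and moderator models, replace the random intercept with an unstructured residual covariance for the three waves, and use Satterthwaite degrees of freedom. The unstructured matrix already carries the between-person variance, so the random intercept is dropped and not kept beside it. Fix this in the text before the data are analysed: the article says that the analysts are not blinded, and a covariance structure chosen after seeing results would be open to question.

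The cost is one line of syntax and six covariance parameters (three variances, three covariances) instead of two, easily estimated with 136 participants. The model remains valid if the correlations prove equal.

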The eHealth self-management application Oncokompas has been developed to support patients and partners of patients with incurable cancer in finding and obtaining optimal supportive care. Oncokompas helps them to monitor their quality of life using patient-reported outcome measures (PROMs), followed by automatically generated tailored feedback, self-care advice, and advice on supportive care services. The content of the version of Oncokompas for partners is focused on self-care of the partner and targets the partner alone instead of the couple (i.e. patient and partner together), for example to inform and advise partners about their shifting roles and responsibilities, their relationship, financial resources, and their work situation. The application is tailored to the partner’s health status and personal preferences. There is a dedicated version of Oncokompas available for patients treated with curative intent [26–28] and for patients with incurable cancer [29]. The aim of this randomized controlled trial (RCT) is to determine the efficacy of Oncokompas as a self-management instrument on caregiver burden, general self-efficacy, and health-related quality of life among partners of patients with incurable cancer and to assess its cost-utility.

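### Five or six potential moderators are each screened at an unadjusted 0.05 and not called exploratory; Bonferroni comes in only after a moderator has been selected

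*Protocol article*

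**What the plan says.** All references are to the Statistical analyses section of the protocol article unless stated otherwise.

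- **Threshold.** "A *p* value < 0.05 will be considered significant for all analyses", followed by "All tests will be one-tailed".
- **Moderators.** Linear mixed models are to establish "whether age, gender, socioeconomic status (e.g. education level and work situation), the health situation of the patient, and baseline quality of life moderate the efficacy". Each model has fixed effects for time and arm, plus "the potential moderator, and all two-way and three-way interaction effects, as well as a random intercept for individuals".
- **Follow-up tests.** Post-hoc analyses are run when the efficacy or moderation models give a significant result. For these, "independent samples t-tests with Bonferroni correction will be used". The same tests are then used inside the levels of a significant moderator: "These tests will also be used to assess whether change scores between the intervention group and control group differed significantly within each category".
- **Outcomes.** The Outcome assessment section names caregiver burden as the primary outcome, with general self-efficacy and health-related quality of life as secondary. The moderation paragraph does not say which of these it applies to.

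Neither this section nor the Discussion calls the moderation analyses exploratory.

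**The concern.** The plan has two stages. The first screens each candidate moderator through its interaction terms, at 0.05 each. The second looks at treatment differences within the categories of any moderator that passed. The stated correction belongs to the second stage only. The statement that a factor moderates efficacy is produced at the first stage, where each of several tests uses the full 0.05 and nothing limits the error over the set.

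The purpose is worded as establishing whether moderation exists, in the same terms as the main efficacy analysis. A reader of the results would therefore have no signal that a single p < 0.05 among several is weak evidence. At stake is a report that Oncokompas works better in one type of partner than in another when no such difference exists, at a rate well above the 5% that the stated threshold suggests.

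**Working it through.** **What the plan gives.** It states no family-wise error rate, so there is none to reproduce. Its one statistical calculation, in the Sample size section, does reproduce. For 0.5 SD, one-tailed alpha 0.05 and power 0.80, the normal approximation is 2 × (1.645 + 0.842)² / 0.5² = 49.5, so 50 per arm. With the t distribution, power is 0.799 at 50 and 0.806 at 51, so 51 per arm is right. Then 51 / 0.75 = 68 per arm and 2 × 68 = 136. That calculation concerns the main effect on the CSI+, not an interaction.

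**Inputs for the moderator screen.**
- Size of each test: 0.05, from the Statistical analyses section.
- Number of tests on one outcome: five as named (age, gender, socioeconomic status, health situation of the patient, baseline quality of life). It is six if the two examples given for socioeconomic status enter as separate variables.
- Assumed: no true moderation, and one interaction test of size 0.05 per moderator.

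**Independent tests.** The chance of at least one false positive among k tests is 1 − 0.95^k.
- k = 5: 1 − 0.7738 = 22.6%; expected number of false positives 5 × 0.05 = 0.25.
- k = 6: 1 − 0.7351 = 26.5%; expected number 6 × 0.05 = 0.30.

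**Correlated tests.** Characteristics such as education and work situation may be related, so independence is the upper case here. Simulating six equicorrelated chi-square statistics on 2 degrees of freedom (arm by two follow-up contrasts by a binary or continuous moderator), each tested at 0.05, gives:

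| Assumed correlation | At least one false positive among six |
|---|---|
| 0 | 26% |
| 0.2 | 26% |
| 0.5 | 21% |
| 0.8 | 14% |

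The correlations are assumptions; the protocol gives none. A moderator with more than two categories would have more degrees of freedom, so these values are illustrative.

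**If moderation were also tested on both secondary outcomes.** There would be 5 × 3 = 15 or 6 × 3 = 18 tests. Under independence that gives 1 − 0.95^15 = 53.7% and 1 − 0.95^18 = 60.3%. With an assumed correlation between outcomes of 0.3 to 0.7 and two-sided tests, the simulated values are about 52% to 44% for five moderators and 59% to 50% for six. The protocol does not state this scope, so these figures show only why the scope should be fixed.

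**Effect of the stated Bonferroni step.** It acts on t-tests that are run only after an interaction has reached 0.05. It can reduce the number of within-category differences declared, but the chance that some moderator passes the screen stays as computed above.

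**The case against.** The strongest reply has three parts.

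First, this is a condensed article, and multiplicity rules and exploratory labels are often left to an analysis plan. That would hold if the article were silent. It is not: it fixes 0.05 for every analysis and says where a correction applies. An analysis plan that adjusted the moderator screen would depart from this text.

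Second, the plan does contain a correction and an ordering of outcomes. Both are true. Bonferroni covers the post-hoc t-tests, and one primary outcome is named and powered. So it would be wrong to say that multiplicity is ignored, and the primary CSI+ test is not inflated by the moderator analyses. Neither fact reaches the screening step.

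Third, the size is moderate. This stands. A reader might infer that a spurious moderator is likely; on the CSI+ alone it is 14% to 26.5%, roughly one in four at most. It reaches about half only if all three outcomes are screened, which the article does not say. A reader might also count six moderators as a minimum; the text names five, and the sixth comes from splitting an example.

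Some wider readings are also tempting. The aim in the Background, "determine the efficacy of Oncokompas as a self-management instrument on caregiver burden, general self-efficacy, and health-related quality of life", might suggest three co-equal outcomes that need a formal gate. The Outcome assessment section ranks them and names the two secondary outcomes, so that does not follow. The placing of quality of life under cost-utility in Table 3 does not unsettle that list, since the same instrument also supplies the QALYs. Nor does the Discussion say that subgroup findings will drive implementation; it speaks of effectiveness for partners in general.

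**Conclusion.** The point holds for the moderation analyses. As written, five or six moderators are screened at an unadjusted 0.05, without an exploratory label, and the only correction starts after selection. With no true moderation, the chance of at least one false-positive moderator on the CSI+ is 22.6% (five tests) to 26.5% (six) under independence, and about 21% to 14% for six tests at assumed correlations of 0.5 to 0.8. It would be higher if the secondary outcomes were screened too.

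These figures rest on no true moderation, one test of size 0.05 per moderator, and assumed correlations. They do not show that a significant moderator in this trial would be mostly noise; that would also need the power of the interaction tests and the frequency of real moderation. The conclusion on the primary outcome stands apart from this point. It is a cheap improvement to what the trial may claim about subgroups.

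**What to change.** In the Statistical analyses section:

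1. Restrict the moderation analyses to the CSI+, or state the outcomes they cover, and fix the list of moderators, including which variables represent socioeconomic status.
2. Call these analyses exploratory. Report the interaction estimate with its 95% CI for every moderator tested, significant or not, and make no claim of moderation from p < 0.05 alone.
3. If a moderation claim is wanted, apply Holm across all moderator interactions before any within-category t-test is opened. The smallest p value would then have to meet 0.05 / 5 = 0.01 with five moderators, or 0.05 / 6 = 0.0083 with six.

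This needs no further data or participants. The cost is that a nominally significant moderator can no longer be presented as established, and that under Holm a real moderator would be harder to declare.
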